### 2.1. Study Design, Setting, and Recruitment

The study involves a double-blinded, randomized, non-inferiority clinical trial [14] with two treatment arms (see Figure 1: study design) conducted at the Institute of Psychiatry, Hospital das Clínicas, São Paulo, Brazil.

Recruitment will be conducted through referrals from physicians in the ECT Service (mainly from the Institute of Psychiatry), self-referral via university community advertisements (e.g., leaflets and email), and advertisements on the website (www.sin.org.br), Google, and social media platforms such as Facebook.

After the recruitment and selection process, participants will undergo a baseline assessment, which includes medical evaluation, neuropsychological assessment, laboratory tests, and cranial MRI. They will then be divided into two groups (ECT and MST). The study will utilize a 1:1 controlled randomization model with blocks of random sizes and lengths generated through www.sealedenvelope.com.

Generally, during the acute phase of ECT, the frequency of treatment sessions varies from one to three times per week. Studies have indicated that ECT conducted twice a week shows comparable efficacy to ECT performed three times a week, while requiring a reduced number of treatments. Additionally, there appears to be greater efficacy of ECT applied three times a week compared to the weekly application schedule [15]. Regarding cognitive functioning, the more frequent the sessions, the greater the cognitive impairments [16]. Consequently, we have opted to conduct ECT or MST sessions during the active phase with a frequency of twice a week on non-consecutive days.

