**Figure 1 biomedicines-11-02150-f001:**
[figure not shown]
Study design (BL ECT, bilateral electroconvulsive therapy; MST, magnetic seizure therapy; HAMD17, Hamilton Depression Rating Scale, 17 items [17]).

Initially, patients will receive a total of 12 sessions, including the first successful titration session. If the first titration session fails to induce adequate seizures, it will not be considered as part of the total number of sessions. After the 12th session, a clinical assessment will be performed. If the patient meets the criteria for remission, defined as a score of 7 or less on the 17-item Hamilton Depression Scale (HAMD17) [17], the sessions will be discontinued, and the patient will undergo a neuropsychological evaluation. If the patient does not achieve remission, they will receive an additional 6 sessions, bringing the total to 18, and will be re-evaluated and undergo a neuropsychological assessment. In this case, regardless of the response or remission, treatment will be discontinued after the 18th session. This is because evidence suggests that the number of sessions required to achieve response and/or remission typically ranges from approximately 6 to 15 sessions [18].

Following the final session, participants will undergo a comprehensive evaluation, including medical assessment, neuropsychological evaluation, laboratory tests, and cranial MRI. Finally, patients will be followed up for 6 months after completing the intervention, with re-evaluations at 3 and 6 months.

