### 2.5. Clinical and Cognitive Measures

All data will be securely stored in an electronic data capture system called Research Electronic Data Capture (REDCap) (https://redcapbrasil.com.br/).

The validated Portuguese versions of the clinical and sociodemographic assessment scales will be applied during screening, at baseline, in the active phase (after the 6th session) and during follow-up (one week, three months, and six months after the last session), as shown in Table 1. The co-primary outcome scales are the HAMD17 [17] and the Autobiographical Memory Task (AMT) [32]. Remission will be defined as a final HAMD17 score less than or equal to 7 points, and a 50% reduction in score compared to baseline assessment will be considered a response. 

Experienced neuropsychologists will perform a cognitive assessment, which will last approximately 120 min, at baseline and at follow-up (one week and six months after the last session), as shown in Table 2.

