### 2.8. Seric Biomarkers

Venous blood collections will be performed in the morning, fulfilling a minimum fasting period of 8 h comprising the following events:C1 (Collection 1): Performed on the day corresponding to the first session, prior to the procedure, taking advantage of the need for venipuncture. This will be considered the baseline sample;C2 (Collection 2): performed prior to 6th session;C3 (Collection 3): performed prior to 12th session;C4 (Collection 4): performed prior to 18th session (if any);C5 (Collection 5): performed 12 weeks after the start of the treatment;C6 (Collection 6): performed 24 weeks after starting treatment, coinciding with the 3-month medical evaluation.

Two 4 mL tubes of venous blood samples with anticoagulant (EDTA) will be collected before each event to prevent biochemical alterations related to the convulsive crisis. The collections will be performed at the ECT Service and immediately transported to the Neuroscience Laboratory LIM-27 for proper storage until the biochemical analysis is conducted. Post-treatment collections (C5, C6, and C7) will be scheduled with the staff and patient at the Neuroscience Laboratory LIM-27 after an 8 h fast. Brain-derived neurotrophic factor (BDNF) will be evaluated in the plasma using an immunofluorescence ELISA technique, which is highly specific for this type of evaluation. This technique has been shown to be more appropriate for state-dependent assessment of BDNF levels than other methods [61].

Our primary objective is to explore potential associations between changes in plasma BDNF levels and variations in depressive symptom scores and treatment response, as well as other clinical and neuroimaging outcomes (such as the variation in volume of each ROI). Additionally, we intend to compare the differences in plasma BDNF variation over time in patients undergoing ECT or MST. Moreover, we will evaluate the discrepancies in BDNF levels between patients who respond positively to treatment and those who do not, in each treatment arm.

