### 2.9. Statistical Analysis

Statistical analyses will be performed in R. The results will be considered statistically significant only if both conditions are met, that is, non-inferiority for the depression outcome, under unilateral *p* < 0.025, and superiority for the cognitive outcome, under *p* bilateral < 0.05. The following groups will be considered: experimental (E), corresponding to MST, and control/comparison (C), corresponding to ECT.

For the co-primary outcome depression (HAMD17), non-inferiority will be assessed by calculating the difference between the means of groups E and C and its 95% confidence interval at the end of the 12th session, which will then be compared to the NI margin (Ha: C-E < NI). Analyses will be performed on modified intent-to-treat (ITT) samples (at least 8 sessions of ECT/MST) and per-protocol (PP).

For the co-primary cognitive outcome (AMT [32]), we will perform linear hierarchical model analyses using a first-order regressive covariance structure, which includes all observed variables without the need to enter data for missing values. The dependent variable is the AMT score [32], the independent variables are time (all observations through week 6) and group. We will test the statistical significance of this interaction according to our superiority hypotheses controlled for age, years of schooling, and treatment-resistant depression (Ha: C-E < 0). Analyses will be performed on the ITT and PP sample.

The same linear hierarchical models will be used for all continuous secondary outcomes. We will assess response and sustained remission, that is, a clinical improvement of symptoms ≥50% (response) and a HAMD17 score ≤7 (remission) at a given point in the study, which will be maintained until the outcome. The trajectories of response and sustained remission between groups will be compared using Kaplan–Meier survival analysis. Response and remission will be compared considering non-inferiority margins of 20% and 15%, respectively. The choice of a 15% non-inferiority margin was based on the consideration that achieving a remission rate of 35% holds clinical relevance in this population with difficult-to-treat depression. Furthermore, this remission rate surpasses those achieved by more conventional and less invasive treatment options for TDR, such as repetitive TMS (rTMS) with an approximate remission rate of 20% [66] and antidepressants with a remission rate of 14% [1].

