## Figures and Tables

**Table 1 biomedicines-11-02150-t001:** Clinical measures.

Measure	Study Period					
	Prior to Acute Phase		Active Phase *	Follow-Up		
	Screening	Baseline		Post-Acute **	3 Months	6 Months
Inform Consent	x					
Demographics Form	x					
ABEP		x				
Medical History Form	x					
ATHF	x					
MINI	x					
QCT		x				
BPI		x				
HAMD17	x	x	x	x	x	x
MADRS		x	x	x	x	x
CGI		x	x	x	x	x
BDI-II		x	x	x	x	
DTS		x	x	x	x	x
BSI		x	x	x	x	x
WHOQOL		x		x	x	x

ABEP, Brazil Criterion of the Brazilian Association of Research Companies 2016 [33]; ATHF, Antidepressant Treatment History Form [22]; MINI, Mini International Neuropsychiatric Interview [19]; QCT, Questionnaire on Childhood Trauma [34]; BPI, Borderline Personality Inventory [35]; HAMD17, Hamilton Depression Rating Scale, 17 items [17]; MADRS, Montgomery–Asberg Scale [36]; CGI, Clinical Global Impression Severity (CGI-S) and Clinical Global Impression Improvement (CGI-I) scales (we will apply both the CGI-S and CGI-I) [37]; BDI-II, Beck Depression Inventory [38]; DTS, Depressive Thoughts Scale [39]; BSI, Beck Suicidal Ideation Scale [40]; WHOQOL, WHO quality of life questionnaire [41]; * after the 6th session; ** one week after the last session (12th or 18th, if applicable).

**Table 2 biomedicines-11-02150-t002:** Neurocognitive measures.

Domain	Measures	Study Period		
		Baseline	Post-Acute	6 Months
Estimated Intelligence Quotient (IQ)	WASI (Vocabulary, Matrix)	x	x	x
Attention/executive functioning; cognitive flexibility and cognitive processing speed	TMT (A & B) and FDT	x	x	x
Verbal and visual episodic memory	RAVLT and BVMT-R	x	x	x
Semantic memory and verbal fluency	FAS	x	x	x
Working memory	Foward and Reverse DGS (WAIS-III)	x	x	x
Cognitive Screening	MoCA	x	x	x
Autobiographical Memory	AMT	x	x	x
Prospective and Retrospective Memory	PRMQ	x	x	x

WASI, The Wechsler Abbreviated Scale of Intelligence [42]; TMT (A and B), Trail Making Test versions A and B [43]; FDT, Five Digit Test [44]; RAVLT, Rey Auditory Verbal Learning Test [45]; BVMT-R, Revised Brief Visuospatial Memory Test [46]; FAS, Verbal Fluency [47]; DGS—WAIS-III, Digit Span—The Wechsler Adult Intelligence Scale, Third Edition-III [48]; MoCA, Montreal Cognitive Assessment [49]; AMT, Autobiographical Memory Task [32]; PRMQ, Prospective and Retrospective Memory Questionnaire [50].

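### The co-primary AMT model stops at an unanchored week 6; counted from treatment start, this leaves out the post-acute AMT of every non-remitter given 18 sessions

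*Protocol article*

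**What the plan says.** Section 2.9 makes success depend on two results: non-inferiority on the HAMD17 and superiority on the AMT. The AMT is analysed with a linear hierarchical model in which "the independent variables are time (all observations through week 6) and group". The test is on the time-by-group interaction, controlled for age, schooling and treatment resistance, in the ITT and PP samples. The covariance structure is described as one "which includes all observed variables without the need to enter data for missing values".

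The schedule is set elsewhere in the article:

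- Section 2.1: sessions are given "with a frequency of twice a week on non-consecutive days".
- Section 2.1, text after Figure 1: for patients in remission after session 12, "the sessions will be discontinued, and the patient will undergo a neuropsychological evaluation". For the others: "If the patient does not achieve remission, they will receive an additional 6 sessions, bringing the total to 18". Their neuropsychological assessment follows the 18th session.
- Section 2.5: cognitive testing takes place "at baseline and at follow-up (one week and six months after the last session), as shown in Table 2". Table 2 lists the AMT at those three visits only.
- Table 1, footnote: the post-acute visit is "one week after the last session (12th or 18th, if applicable".

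Section 2.9 does not say from which day week 6 is counted.

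**The concern.** The rule on which observations enter the co-primary model does not fit the visit schedule. Each patient has one acute post-baseline AMT, and its date depends on whether the patient was in remission at session 12. A calendar cut-off near the end of the 12-session course therefore sorts patients by their depression result.

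Two things are at stake. First, if only session-12 remitters supply a post-baseline AMT, the arms are compared in subgroups formed after randomisation by the scale that serves as the other co-primary outcome. Randomisation no longer protects that comparison, and it says nothing about the patients who had the longest courses. Second, section 2.10 accepts a wide HAMD17 margin of 5.7 points because cognitive superiority must also be shown, so the AMT test carries much of the argument. If the meaning of week 6 is settled only after the data are seen, the choice of sample stays open.

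**Working it through.** **The plan's own sample size.** Section 2.10 gives margin 5.7, SD 9.5, one-sided alpha 0.025 and power 80%. Per arm: 2 × (1.96 + 0.84)² × (9.5/5.7)² = 2 × 7.85 × 2.78 = 43.6, so 44 per arm and 88 in total. The stated figure reproduces and does not depend on this point.

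**Calendar.** Let day 0 be the first counted session. With two sessions a week on non-consecutive days, the gap g within a week is 2 to 5 days. An even-numbered session S falls on day (S/2 − 1) × 7 + g, and the post-acute AMT is 7 days later.

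| Course | Last session | Post-acute AMT | Weeks |
|---|---|---|---|
| 12 sessions | 35 + g = day 37-40 | day 44-47 | 6.3-6.7 |
| 18 sessions | 56 + g = day 58-61 | day 65-68 | 9.3-9.7 |

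**Readings of week 6.**

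1. From treatment start, ending on day 42. No patient tested a week after session 12 or 18 qualifies. Session 11 falls on day 35, and 35 + 7 = 42, so only patients who stop by session 11 could.
2. From treatment start, taken loosely as days 42-48. Remitters at session 12 (day 44-47) enter. An 18-session patient misses by at least 65 − 48 = 17 days.
3. Remitters tested directly after session 12, as the text after Figure 1 could be taken to allow. They would be tested from day 37-40, but non-remitters are not tested before session 18, on day 58 at the earliest.
4. A label for the post-acute visit, or weeks counted from the last session. All post-acute AMTs enter and the 6-month AMT does not.

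Counting from the baseline assessment instead of the first session only moves the AMT later. A cut-off from treatment start that admits every scheduled post-acute AMT would have to be day 68 or later.

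**Patients affected under reading 2.** The share without a post-baseline AMT is 1 minus the session-12 remission rate. The document does not give that rate, so a range is assumed. The 35% is the rate that section 2.9 calls clinically relevant, used only as an illustration.

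| Assumed remission | Left out, of 44 per arm |
|---|---|
| 20% | 35.2 |
| 35% | 28.6 |
| 50% | 22.0 |
| 60% | 17.6 |

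**Power** (two-sample t-test, two-sided 0.05). The difference detectable with 80% power is 0.60 SD with 44 per arm, 0.86 SD with 22 and 1.06 SD with 15. At the planned effect of 1.31, 15 per arm still give 93% power.

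**Selection shift, illustrative.** Assume that depression improvement and AMT change are bivariate normal with correlation rho, and that remitters are the upper tail of improvement. Assume remission of 35% with MST and 50% with ECT, a gap equal to the 15% remission margin. Mean improvement among remitters, in SD units, is φ(z)/p: 0.370/0.35 = 1.058 with MST and 0.399/0.50 = 0.798 with ECT. The difference is 0.260, so the remitter-only AMT contrast moves by 0.260 × rho in favour of MST: 0.026, 0.078 and 0.130 SD for rho of 0.1, 0.3 and 0.5. With equal remission the shift is zero.

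**The case against.** The strongest reply is that week 6 was never meant as a day count from the first session. Section 2.5 and the Table 1 footnote time the post-acute visit from the last session. On that clock a six-week limit admits every post-acute AMT, after 12 or 18 sessions, and removes only the 6-month test. The same holds if week 6 is shorthand for the end of the acute phase. It would therefore be wrong to infer that no reading admits the 18-session patients: two do.

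A reader might also infer that the model has no post-baseline data from anyone who completes a course. That follows only from the strict day-42 reading, which would defeat the interaction test that section 2.9 sets up, so it is unlikely to be intended. Nor does any sentence expressly exclude non-remitters; the stated ITT sample points the other way.

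Section 2.8 does count from treatment start ("performed 12 weeks after the start of the treatment"), but that is the blood-sampling schedule. It also equates 24 weeks from the start with the 3-month evaluation, which by the calendar above falls at about 18-19 or 21-22 weeks. It is weak support for dating the AMT.

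Finally, a condensed article may leave visit windows and the coding of time to the full protocol or the SAP. That would answer a complaint about missing detail. Here a cut-off is stated, and on its natural reading it contradicts the schedule. The appeal to the model's handling of missing values does not help either. The values are observed and then cut off, the cut-off depends on the session-12 HAMD17, and a baseline value alone adds no information on change.

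**Conclusion.** The conflict is in the text. Counted from treatment start, which is the natural reading because 12 sessions at two a week nominally take six weeks, the rule removes the post-acute AMT of every non-remitter given 18 sessions. Among patients who complete a course, at best the session-12 remitters remain. The comparison is then selected on a depression outcome that arises after randomisation, and it does not match the stated ITT sample. The two readings that avoid this are plausible, but neither is written down.

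The calendar is firm. The size of the bias is not: it depends on remission rates and a correlation that the document does not give. Under the assumed inputs it is modest (0.03-0.13 SD against a planned 1.31), and it is zero if remission is equal in both arms. A reader might infer that the co-primary test is underpowered or seriously biased; the figures show neither. The weakness is an undefined comparison in a result that decides the trial, and it should be settled before the data are seen.

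**What to change.** In section 2.9, replace the week-6 limit with the scheduled visits. Define the co-primary AMT contrast as the between-arm difference in change from baseline to the post-acute visit, one week after the last session whether that is the 12th or the 18th, for all patients in the analysis set. Any display by course length should be descriptive, because course length depends on remission after randomisation.

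This is a change of wording: no extra visits, tests or patients, and no change to alpha. The downside should be stated in the plan. The contrast pools two course lengths and two visit times about three weeks apart (day 44-47 and day 65-68), whereas the planning effect of 1.31 in section 2.10 is after 12 sessions. With 44 per arm, 80% power holds down to 0.60 SD, under half of 1.31, so there is room for dilution. Testing everyone after session 12 would match the planning figure but adds a test session for non-remitters.

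### The AMT superiority test is a change-score comparison that uses baseline AMT less efficiently than baseline adjustment, and age and schooling as main effects would add little to it

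*Protocol article*

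**What the plan says.** Section 2.9 of the protocol article defines the co-primary cognitive analysis as a mixed model with first-order autoregressive covariance, fitted to the observed data without imputation. On its terms it says: "The dependent variable is the AMT score [32], the independent variables are time (all observations through week 6) and group". On the test it says: "We will test the statistical significance of this interaction according to our superiority hypotheses controlled for age, years of schooling", and it adds treatment resistance as a third covariate. The superiority requirement is "superiority for the cognitive outcome, under *p* bilateral < 0.05", and it must be met together with HAMD17 non-inferiority for the trial to succeed.

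Section 2.5 schedules the cognitive battery "at baseline and at follow-up (one week and six months after the last session), as shown in Table 2", and that table lists AMT at all three times. Baseline AMT is thus collected from every patient and enters the model as an outcome observation. It is not named as a covariate. The article does not say whether age and schooling enter as main effects only or also by time.

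The approach reaches beyond AMT: "The same linear hierarchical models will be used for all continuous secondary outcomes".

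**The concern.** Two features of the stated model work against precision.

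- With group, time and their interaction all in the model, each arm has its own baseline mean. The interaction is then the arm difference in mean change. Randomisation makes the true baseline means equal, and the model does not use that fact.
- Age and schooling do not vary between visits. As main effects they move a patient's whole AMT profile up or down and drop out of the change. A reader would expect control for these variables to sharpen the comparison and to allow for chance imbalance. In complete data, main effects do neither for the interaction.

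AMT superiority is half of the success rule, and section 2.10 accepts a wide HAMD17 margin partly because cognitive superiority must also be shown. The planned AMT effect comes from one unpublished trial of 75 patients. The continuous secondary outcomes inherit the same model, and the article states no effect size for them.

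**Working it through.** **The plan's own figures (section 2.10).**
- HAMD17 non-inferiority: margin 5.7, SD 9.5, one-sided alpha 0.025, power 80%. Per arm, n = 2 × 9.5² × (1.960 + 0.842)² / 5.7² = 43.6, so 44, or 88 in total. This matches.
- AMT: effect 1.31, two-sided alpha 0.05. At 90% power, n = 2 × (1.960 + 1.282)² / 1.31² = 12.2, so 13 per arm, or 26 in total. This matches the stated 26. At 80% power the same formula gives 20. The article states no separate power for AMT.

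**What the interaction estimates.** Take baseline (visit 0) and the post-acute visit (visit 1). With group G and a time-invariant covariate z as a main effect:
- Y0 = a + bG + cz + e0
- Y1 = a + t + (b + d)G + cz + e1
- Y1 − Y0 = t + dG + (e1 − e0)

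The covariate term cancels, and d, the interaction, is the arm difference in mean change. The third covariate behaves alike. A current treatment-resistant episode is an inclusion criterion (section 2.3), so a yes/no indicator is constant. Degree of resistance at entry would be another time-invariant trait.

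**Numerical check of the covariates.** Two visits, 50 per arm, true effect 0.50 SD, rho 0.6, REML, 400 simulated trials, two time-invariant covariates:
- Complete data: with and without the main effects, estimates agree to 1e-14 and standard errors to a relative 3e-8.
- About 10% of post scores missing, with dropout assumed to depend on covariate and arm: the main effects shift the estimate by 0.034 SD on average and 0.13 SD at most. The mean estimate is 0.469 without them and 0.503 with them.
- About 20% missing: mean shift 0.058 SD, maximum 0.20 SD; mean estimates 0.457 and 0.515.
- Covariate-by-time terms shift the estimate even in complete data, by up to 0.13 SD.

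**Precision.** Work in units of the SD of a single AMT score, taken as equal at both visits, with rho the baseline-to-post correlation. The article gives no rho, so a range is assumed. The variance factor is 2(1 − rho) for the interaction and 1 − rho² for ANCOVA; their ratio is (1 + rho)/2. The difference detectable at 80% power is 2.8016 × √(factor × 2/44).

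| rho | Interaction factor | ANCOVA factor | Ratio | Detectable, interaction | Detectable, ANCOVA |
|---|---|---|---|---|---|
| 0.3 | 1.40 | 0.91 | 0.65 | 0.71 | 0.57 |
| 0.5 | 1.00 | 0.75 | 0.75 | 0.60 | 0.52 |
| 0.6 | 0.80 | 0.64 | 0.80 | 0.53 | 0.48 |
| 0.7 | 0.60 | 0.51 | 0.85 | 0.46 | 0.43 |
| 0.8 | 0.40 | 0.36 | 0.90 | 0.38 | 0.36 |

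The standard error is smaller by 1 − √0.65 = 19% at rho 0.3 and 1 − √0.90 = 5% at rho 0.8. In the complete-data simulation at rho 0.6, the empirical SD was 0.155 for ANCOVA and 0.171 for the interaction. The variance ratio is 0.155²/0.171² = 0.82, against 0.80 in theory.

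**Power at the planned effect.** Worst case in the range, rho 0.3, 44 per arm: standard error √(1.40 × 2/44) = 0.252, so 1.31/0.252 = 5.19 and power is 99.9%. Under ANCOVA it is about 100%. If 1.31 was expressed in SDs of change, the factor is 1.00 and power is again above 99.9%.

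**Visit window.** Section 2.9 limits the model to observations through week 6. Twelve sessions at two per week end at about week 6, and the post-acute AMT comes one week after the last session. The working takes the post-acute visit as the intended endpoint; the window is a separate matter to reconcile.

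**The case against.** The strongest reply is that nothing here is wrong. A group-by-time interaction is a valid, unbiased and widely used randomised comparison. The article condenses a fuller protocol, and how covariates enter a mixed model is detail that such an article may leave out. All of that stands, and it is why the point concerns efficiency and clarity.

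A reader might infer four stronger things, none of which the document supports:

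- **That the covariate adjustment does nothing.** This is exact only for main effects in complete data. The plan allows 10% for attrition and chooses a model that uses patients with missing visits: "we will perform linear hierarchical model analyses using a first-order regressive covariance structure, which includes all observed variables without the need to enter data". Under the dropout assumed above, the main effects moved the estimate and brought its mean closer to the truth. The text also does not exclude by-time terms, which would act in complete data.
- **That chance imbalance in age or schooling biases the test.** Under 1:1 randomisation, chance imbalance is random error that the standard error and type I error rate already cover. Adjustment could reduce that error if age or schooling predicts AMT change, and the article gives no evidence on whether they do.
- **That baseline AMT is discarded.** It is in the model as an outcome, and the test compares change from it. It is used less efficiently than it could be.
- **That the co-primary is underpowered.** At the planned effect it is not, under either analysis.

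The efficiency point survives because the article does fix the outcome, the predictors and the interaction as the test. Under those terms the variance ratio follows.

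**Conclusion.** The AMT test as stated is valid but less precise than a baseline-adjusted comparison. The variance under baseline adjustment is 65% to 90% of that of the interaction. This rests on an assumed rho of 0.3 to 0.8, equal variances at the two visits and a free baseline mean per arm. With 44 per arm, the effect detectable at 80% power would fall from 0.71 to 0.57 SD at the low end of that range and from 0.38 to 0.36 SD at the high end. If age and schooling are main effects only, they act solely through missing visits and so do little for precision or chance imbalance.

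At an effect of 1.31 the choice has no practical effect on power. The gain is real only if the true AMT effect is much smaller, or for the continuous secondary outcomes. This is a free or cheap improvement to make before unblinding, not a defect that invalidates the co-primary.

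**What to change.** Change the AMT analysis in section 2.9 to one of the following.

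- **Preferred, because it keeps the plan's use of all observed data:** retain the repeated-measures model, constrain both arms to a common baseline mean, and enter age-by-time and schooling-by-time terms.
- **Simpler:** ANCOVA of post-treatment AMT on arm, baseline AMT, age and years of schooling.

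Under either, report the adjusted arm difference at the post-treatment visit with its 95% CI, and state how each covariate enters. Use the same form for every continuous secondary outcome that has a baseline value.

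The cost is a sentence or two of text, no new data and a few degrees of freedom. By-time terms lose a little precision where the covariates do not predict change: in the complete-data simulation, where they did not, the empirical SD of the unconstrained interaction rose from 0.171 to 0.174. ANCOVA has the further drawback that only patients with a post-treatment score contribute. Age and schooling should stay in it: ANCOVA on baseline alone gave a mean of 0.470 against a true 0.50 in the simulation with about 10% missing.

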### 2.6. Safety Monitoring

Pre-anesthetic and dental evaluation will be performed before the start of the sessions. Adverse events and safety will be monitored and recorded at every study visit. To assess any adverse effects during and after the active phase of treatment, we will use the Non-Cognitive Adverse Effects Questionnaire for ECT/MST [51], which evaluates symptoms such as headaches, muscle aches, nausea, prolonged seizures, and severe events. We will also use the Young Mania Rating Scale (YMRS) [52] to assess the occurrence of (hypo)manic induction. Additionally, the Orientation Scale, a 10-item questionnaire, will be administered 30 min after each seizure treatment. Sobin et al. [53] found a positive correlation between postictal reorientation time and retrograde amnesia. If any harm occurs as a result of study participation, appropriate care will be provided to participants.

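### If the group-by-time rule for continuous secondary outcomes is applied to the Orientation Scale, which is rated only after treatment, it tests drift across sessions and not the difference between MST and ECT

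*Protocol article*

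**What the plan says.** Section 2.9 (Statistical Analysis) describes the model for the co-primary cognitive outcome, AMT. It is specified as "linear hierarchical model analyses using a first-order regressive covariance structure", and "the independent variables are time (all observations through week 6) and group". The term to be tested is named: "We will test the statistical significance of this interaction according to our superiority hypotheses". The next paragraph extends this model: "The same linear hierarchical models will be used for all continuous secondary outcomes". No exception is made for measures without a baseline, and no other term is named as the tested effect.

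Section 2.6 (Safety Monitoring) states that "the Orientation Scale, a 10-item questionnaire, will be administered 30 min after each seizure treatment". No rating before the first treatment is described, and the scale is in neither Table 1 nor Table 2.

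Table 1 has a single CGI row, ticked at baseline and at every later visit. Its footnote says "we will apply both the CGI-S and CGI-I" and does not say which of the two the baseline tick refers to.

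**The concern.** A group-by-time interaction measures a treatment effect when the first observation precedes treatment: the arms start level by randomisation, and any later separation appears as a change in the arm difference. When every observation is made after treatment, the first rating already contains the effect. The effect is then the difference in level between the arms, and the interaction shows only whether that difference grows or shrinks.

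The Orientation Scale is such a measure. It bears on a stated aim of the trial: the Introduction cites faster reorientation as an MST advantage, and section 2.6 supports the scale by a reported correlation between reorientation time and retrograde amnesia. If the section 2.9 rule is followed for it, a steady acute benefit of MST could not be found by the named test. A significant result would describe a trend over the course and not the size of the benefit.

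**Working it through.** **Inputs from the protocol article**
- Tested term, factors and covariance: section 2.9, as quoted above. The printed covariance is read as first-order autoregressive; its correlation is not given.
- Ratings: one per session. "Initially, patients will receive a total of 12 sessions, including the first successful titration session" (section 2.1). Sessions run "with a frequency of twice a week on non-consecutive days", so 12 / 2 = 6 weeks, which matches the model's week-6 window.
- Sample size: section 2.10 gives 88 before attrition, and this reproduces: n per arm = 2 × (1.96 + 0.84)² × 9.5² / 5.7² = 43.6, rounded up to 44, total 88. The plan gives no power figure for the secondary-outcome models.

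**Assumptions, not in the document**
- Size of the Orientation Scale difference, its SDs and the correlation between sessions.

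**Step 1: what the interaction measures.** Let D(t) be the MST-minus-ECT difference in mean score at session t. With session as a factor, the interaction tests D(t) − D(1) = 0 for t = 2 to 12; with linear time it tests the slope of D. If D(t) = d at every session, both are zero for any d. Example: means of 9 (MST) and 8 (ECT) at every session give D = 1 throughout and an interaction of 1 − 1 = 0. The rejection rate is then the nominal 5%, whatever the effect size, correlation or coding of time. A simulation (0.8 SD, correlation 0.5, 50 per arm, 12 ratings, 5,000 runs) gave 4.7%.

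**Step 2: a changing difference.** Suppose, for illustration, that D falls evenly from 1.5 points at session 1 to 0.5 at session 12. The slope is (0.5 − 1.5) / 11 = −0.09 per session, while the mean difference is (1.5 + 0.5) / 2 = 1.0 in favour of MST. The interaction points against MST although MST is better at every session.

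**Step 3: power of the mean-level difference, random-intercept illustration.** Between- and within-patient SD 1.5 each, 12 sessions, 44 per arm:
- Variance of a patient's mean = 1.5² + 1.5² / 12 = 2.25 + 0.1875 = 2.4375.
- SE of the arm difference = √(2.4375 × 2 / 44) = 0.333.
- Power ≈ Φ(d / 0.333 − 1.99), two-sided 5%, 86 df.

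| Constant difference d | Mean-level test | Interaction test (simulated) |
|---|---|---|
| 0.8 | about 66% | 5.1% |
| 1.0 | about 85% | 4.7% |
| 1.5 | about 99% | 5.8% |

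**Step 4: the same under the plan's covariance.** For an autoregressive structure with unit SD, the generalised least squares SE of the mean difference is √[(2/n) × (1 + ρ) / (T(1 − ρ) + 2ρ)]. With T = 12, n = 44, ρ = 0.7: √[0.04545 × 1.7 / 5.0] = 0.124. For d = 0.5 SD: 0.5 / 0.124 = 4.02, and power = Φ(4.02 − 1.96) = 98%. Over d = 0.5 to 1.0 SD and ρ = 0.3 to 0.7, power is 98% to 100%. The interaction stays at 5%.

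**Step 5: how far the problem reaches.** Adding a baseline that is equal between arms (baseline plus two post-treatment ratings) turns the same constant advantage into an interaction. Power of the interaction test is then 46% to 84% at 0.5 SD and 87% to nearly 100% at 0.8 to 1.0 SD (44 to 50 per arm). The difficulty is confined to measures with no usable baseline.

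**The case against.** The strongest objection is that the article never calls the Orientation Scale a secondary outcome. It appears once, under Safety Monitoring. The secondary outcomes named in the Discussion are response, remission and neuropsychological testing, and every Table 2 measure has a baseline. A condensed article may leave the analysis of a safety scale to the full plan. This stands, and it makes the point conditional. A reader might infer that the plan expressly prescribes the interaction for this scale; it does not. But the scale is numeric and rated per session, and section 2.9 gives the chi-square test only to adverse events, (hypo)manic episodes and treatment guessing. The linear model is the only stated method that fits it.

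Second, group is itself in the model, and the superiority hypothesis is written as a difference between arms, so the level difference can be estimated from the same fit. This also stands. A reader might infer that a real benefit would be reported as no difference; that follows only if the interaction alone is reported. The plan nevertheless names the interaction as the test.

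Third, exact constancy is a special case. Session 1 is a titration session and the stimulus changes afterwards (sections 2.4.2 and 2.4.3), so the arm difference may move. That is fair, but it gives the interaction power against drift without making it an estimate of the benefit.

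Fourth, the power figures in step 3 assume normal scores. If the 10 items are scored to 10 (an assumption), a mean of 9 and a total SD of √(1.5² + 1.5²) = 2.12 put about 32% of simulated MST scores above the maximum. Those figures are illustrative only. The zero in step 1 does not depend on them.

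A reader might also extend the point to CGI-I as a measure with no baseline. Table 1 does not show that: one row covers both CGI scales and is ticked at baseline. That CGI-I cannot have a baseline value is an inference from its being an improvement rating, and if a fixed no-change value were entered there, the interaction would recover the effect.

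**Conclusion.** The point holds in a limited, conditional form. As written, the only stated method that suits the Orientation Scale tests whether the arm difference changes across sessions. Against a stable MST advantage its rejection rate is 5% whatever the size of the advantage; this is algebra and needs no assumption about SD or correlation. Against a changing advantage it reports drift, possibly of the opposite sign. The contrast with 85% power, or 98% to 100%, for the mean-level difference rests on assumed effect sizes, SDs and correlations and shows only the order of the loss.

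The consequence is at secondary or safety level. HAMD17, AMT and all Table 2 measures have baselines and are untouched. For CGI-I the document supports a request for clarification and no more.

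**What to change.** Add one sentence to section 2.9: for measures rated only after treatment (the Orientation Scale), the tested quantity is the between-arm difference in mean level, averaged over sessions 1 to 12, from the same mixed model with session as a factor. Limiting the average to 12 sessions keeps it to the part of the course planned for everyone, since only non-remitters go on to sessions 13 to 18. Keep the interaction for outcomes with a baseline.

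Add a footnote to Table 1 stating whether the baseline CGI tick refers to CGI-S only. If CGI-I has no baseline rating, compare the arms by level at the post-treatment rating.

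The cost is one sentence and one footnote. No new data, visits or patients are needed, and no other analysis changes.
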